## **2.2 Description of XIENCE V EECSS**

One of the test devices used in the SPIRIT WOMEN Clinical Evaluation is XIENCE V Everolimus Eluting Coronary Stent System (XIENCE V EECSS). The XIENCE V EECSS has received CE mark approval on 30 January 2006 and FDA approval 02 July 2008. In this Clinical Investigation Plan (CIP), the following abbreviations are used with regards to the XIENCE V.

**Table 2.2: Abbreviations of XIENCE V Everolimus Eluting Coronary Stent System**

|                |                                    |
|----------------|------------------------------------|
| XIENCE V EECSS | System (stent and delivery system) |
| XIENCE V EECS  | Stent                              |
| XIENCE V       | Product in General                 |

The XIENCE V EECSS is manufactured by Abbott Cardiovascular Systems, Inc., California, an affiliate of Abbott Vascular Inc. The XIENCE V EECSS is comprised of the ML VISION® Stent (2.75, 3.0 mm, 3.5, 4.0 mm) or the ML MINI VISION® Stent (2.25, 2.5 mm) (EC 71619) on a delivery system (EC 71619) and a drug eluting coating.

The XIENCE V EECSS is a balloon expandable stent, fabricated from a single piece of medical grade L-605 Cobalt Chromium (CoCr) alloy and is similar in strut design to the ACS ML VISION® Stent and ML MINI VISION® Stent. The ML VISION® and the ML MINI VISION® stents are based on the same design principle as the ACS ML TETRA™ Stent (EC 54315). The ML VISION® and the ML MINI VISION® stents are balloon expandable stents that consist of serpentine rings connected by links.

Figure 2.2.1 Xience V Stent

[figure not shown]

To maintain stent radiopacity with a thinner strut thickness, the ML VISION® and the ML MINI VISION® stents are made of L-605 CoCr alloy instead of the 316L Stainless Steel material used for the ACS ML TETRA™ Stent. The doses of everolimus on the XIENCE V EECSS are presented in the IFU of XIENCE V.

### **2.2.1 The XIENCE V EECSS Delivery System**

The XIENCE V EECSS Delivery System is similar to the ML VISION® RX CSS and the ACS ML RX ZETA™ CSS (EC 60607) in delivery system design, performance specifications and material.

Like other ACS RX Coronary Stent Systems and Coronary Dilatation Catheters, the XIENCE V EECSS combines a single lumen proximal shaft with a dual lumen mid-shaft and a co-axial lumen distal shaft to create the rapid exchange capability. The single lumen proximal shaft connects the intermediate/distal shaft with the inflation port of the catheter. The guide wire exit notch is located at the proximal end of the junction between the intermediate shaft and the mid-shaft support. The overall length of the catheter is 143 cm.

Two radiopaque balloon markers are located on the distal segment of the inner member and are positioned to mark the working length of the balloon. The stent is mounted such that the markers reflect the expanded stent length. The radiopaque markers aid in positioning the stent fluoroscopically and also aid in accurately positioning the delivery system for post-deployment dilation, if necessary.

There are two non-radiopaque markers on the proximal shaft of the XIENCE V EECSS. These two markers, located 95 cm and 105 cm proximal to the distal tip, indicate when the distal tip of the catheter

exits the tip of a brachial or femoral guiding catheter, respectively. These markers can be visually tracked on the shaft as the catheter enters the sheath.

A single arm adapter is attached to the proximal end of the catheter and accesses the inflation/deflation lumen. The proximal shaft is thermally bonded to a nylon adaption cup, and the adaption cup is mechanically sealed to the single arm adapter with a polycarbonate nosepiece, which is threaded onto the single arm adapter and bonded together with methylene chloride.

A 0.014-inch or smaller diameter guide wire can be used in the guide wire lumen. The guide wire exits the guide wire lumen at the guide wire exit notch, which is formed at the junction of the mid-shaft and the intermediate shafts. Proximal to this point, the guide wire runs externally alongside the proximal shaft of the catheter.

### **2.2.2 The XIENCE V EECSS Polymer Coating**

The XIENCE V EECSS has a drug eluting coating consisting of two polymers and the drug everolimus. The coating is composed of acrylic and fluoro polymers, both previously approved for use in blood contacting applications. These materials are components of vascular sutures and other drug eluting coronary stents.

### **2.2.3 The Anti-proliferative Drug: Everolimus**

Everolimus [40-O-(2-hydroxyethyl)-rapamycin], which is provided to Abbott Cardiovascular Systems, Inc. by Novartis Pharmaceuticals Corporation, is a semisynthetic macrolide immunosuppressant, from the same family as Rapamycin (INN: sirolimus). Everolimus is approved in the EU and marketed as Certican.

Further information regarding everolimus pre-clinical and clinical data can be found in the investigator's brochure.

## **2.3 Description of XIENCE PRIME EECSS**

The second test device used in the SPIRIT WOMEN Clinical Evaluation (RSS only) is XIENCE PRIME Everolimus Eluting Coronary Stent System (XIENCE PRIME EECSS). The XIENCE PRIME EECSS has received CE mark approval on 23 June 2009. The XIENCE PRIME EECSS is manufactured by Abbott Cardiovascular Systems, Inc., California, an affiliate of Abbott Vascular Inc.

The XIENCE PRIME stent system is similar to that of the Abbott Vascular XIENCE V Everolimus Eluting Coronary Stent System (EECSS) (CE Mark, January 2006). The XIENCE PRIME stent uses the identical stent, balloon material, and drug coating formulation as the XIENCE V stent. However, the XIENCE PRIME stent design has been slightly modified from that of the XIENCE V stent in order to accommodate design improvements while not affecting the overall structural integrity of the design. These modifications include longer cell length for optimized stent retention, taller non-linear links for improved flexibility, straighter bar arms to reduce strut interference and to better maintain coating integrity during the crimping process, and a modified proximal end ring to reduce strut lifting. The delivery system utilizes the same principle of operation as other Abbott Vascular Rapid Exchange (RX) coronary stent systems and coronary dilatation catheters.

There are two stent designs for the XIENCE PRIME stent. The small XIENCE PRIME stent design is intended for the 2.25, 2.5 and 3.0 mm expansion diameters while the medium XIENCE PRIME stent design is intended for the 3.5 and 4.0 mm expansion diameters.

## **2.4 Description of the CYPHER SELECT™ Plus**

The CYPHER SELECT™ Plus Sirolimus-eluting Coronary Stent (Cordis Corporation) is to be used as an active-control device in the randomized sub-study. CYPHER uses Sirolimus as an anti-proliferative drug and obtained FDA approval in 2003 and is commercially available throughout Europe and international markets including the United States. In the event a subsequent generation of CYPHER SELECT™ Plus Sirolimus-eluting Coronary Stent is released during the course of the study, it may replace the CYPHER SELECT™ Plus Sirolimus-eluting Coronary Stent.

## **3 CLINICAL EVALUATION OBJECTIVE**

The objective of this clinical evaluation is a continuation in the assessment of the performance of the XIENCE EECSS with the primary focus on clinical outcomes in the treatment of female patients with de novo coronary artery lesions. The study will also provide characterization of the female population undergoing stent implantation with the XIENCE EECSS.

## **4 CLINICAL EVALUATION DESIGN**

The SPIRIT WOMEN Clinical Evaluation is a prospective, open label, single arm, multi-center study evaluating performance of the XIENCE V EECSS in the treatment of female patients with coronary artery lesions, per its Instructions for Use (IFU). Additionally, this study will include a prospective, single-blind, double arm, randomized multi-center sub-study comparing the XIENCE EECSS (XIENCE V EECSS and XIENCE PRIME EECSS) to the CYPHER SELECT™ Plus Sirolimus-eluting Coronary Stent in the treatment of female patients with coronary artery lesions.

- Approximately 1550 patients will be enrolled in the single arm study (SPIRIT WOMEN Single Arm Study).
- Approximately 450 patients will be randomized 2:1 (XIENCE EECSS vs. CYPHER SELECT™ Plus Sirolimus-eluting Coronary Stent) from up to 35 selected sites (randomized sub-study).

The test device used is XIENCE Everolimus Eluting Coronary Stent System (XIENCE V EECSS and XIENCE PRIME EECSS (randomized sub-study only)). The XIENCE V EECSS has received CE mark approval on 30 January 2006 and FDA approval 02 July 2008. The XIENCE PRIME EECSS has received CE mark approval on 23 June 2009.

The control device used in the randomized sub-study is CYPHER SELECT™ Plus Sirolimus-eluting Coronary Stent. In case a subsequent generation of CYPHER SELECT™ Plus Sirolimus-eluting Coronary Stent is released during the course of the study, it may replace the CYPHER SELECT™ Plus Sirolimus-eluting Coronary Stent.

Assessment of anginal status, collection of data regarding adverse events, details of any subsequent coronary interventions, Clinical Investigation Plan (CIP) medications use and changes in concomitant medications will be collected at 30 days, 240 days and 1, 2, 3, 4 and 5 years post-procedure for all patients.

Evaluation of specific female demographics such as menopausal, hysterectomy and oophorectomy status, past and current use of hormonal contraceptives, and use of weak estrogens will occur for all patients.

### **4.1 Patient Follow-up**

All patients will have clinical follow-up at 30 days, 240 days and at 1, 2, 3, 4 and 5 years.

A subgroup of approximately 450 patients will have angiographic follow-up at 270 days (patients in the randomized sub-study).

## **4.2 Treatment Strategy**

### **The treatment strategy for all patients enrolled in the clinical evaluation is as follows:**

The treatment strategy will be determined by the Investigator. It is recommended that each enrolling investigator review the most recent IFU to assess contraindications, warnings, and precautions for treating potential patients.

Loading dose of clopidogrel of at least 300 mg prior to the start of the procedure. This dose may be adjusted if the patient is already taking clopidogrel. Recommended prior to the start of the procedure, however no later than 1 hour post procedure.

No non-study percutaneous procedures can be performed at the time of the study procedure

### **Additional treatment strategy for patients enrolled in the Single Arm Study is as follows:**

After meeting the general and angiographic inclusion and exclusion criteria, the target lesions should be treated by stenting with the XIENCE V EECSS according to the IFU.

Registration should only be done after confirmation of the angiographic inclusion criteria and before implantation of the first stent.

All lesions should be planned to be treated with the XIENCE V.

If any staged procedures are planned at baseline, it is necessary that the investigator treats the enrolled patients with only XIENCE V EECSS during the planned staged procedure.

Bailout stenting should be performed with XIENCE V EECSS of appropriate length.

It is recommended that all patients should receive  $\geq 75$  mg of aspirin daily for a minimum of five years following the procedure.

It is recommended that treatment with clopidogrel should be continued at 75 mg daily for a period of at least 6 months. Ticlopidine at a dose standard with hospital practice may be substituted for clopidogrel, as required by hospital practice or if the patient develops hypersensitivity to clopidogrel.

### **Additional treatment strategy for patients enrolled in the randomized sub-study is as follows:**

The test devices used are the XIENCE V Everolimus Eluting Coronary Stent System (XIENCE V EECSS) and the XIENCE PRIME Everolimus Eluting Coronary Stent System (XIENCE PRIME EECSS).

After meeting the general and angiographic inclusion and exclusion criteria, the target lesion(s) should be treated according to the same randomization schedule. If two or more target lesions are to be treated, all lesions must receive the treatment that has been assigned as per the randomization.

If two or more target lesions are to be treated and the patient is randomized to the XIENCE EECSS, all lesions must receive either the XIENCE V EECSS or the XIENCE PRIME EECSS.

Randomization should be done only after confirmation of the angiographic inclusion criteria and before implantation of the first stent. Once randomization is completed and a treatment is assigned, crossover is not permitted.

If it is not possible to implant the stent allocated by randomization, it is recommended that any other commercially available stent, either BMS or DES be implanted, rather than the XIENCE or the CYPHER SELECT™ Plus Sirolimus-eluting Coronary Stent.

If bailout stenting is necessary, the stent used should be the same as allocated by randomization for the index procedure, and should be used according to the Instructions for Use (IFU).

If any staged procedures are planned at baseline, it is necessary that the investigator treats the enrolled patients with the same study stent during the planned staged procedure as was used at baseline (as allocated at randomization).

All patients should receive  $\geq 75$  mg of aspirin daily for a minimum of five years following the procedure.

All patients should receive clopidogrel 75 mg daily for a period of at least 6 months. Ticlopidine at a dose standard with hospital practice may be substituted for clopidogrel, as required by hospital practice or if the patient develops hypersensitivity to clopidogrel.

#### **Treatment strategy for the CYPHER SELECT™ Plus Sirolimus-eluting Coronary Stent**

Use of the CYPHER SELECT™ Plus Sirolimus-eluting Coronary Stent should be according to its Instructions for Use.

#### **4.3 Measures to be taken to Avoid/Minimize Bias**

A centralized randomization/registration service will be used. Randomization/registration should be done only after confirmation of angiographic inclusion criteria and before implantation of the first stent. Once randomized/registered the patient is considered enrolled in the study.

A subset of approximately 450 patients will be randomized in a 2:1 ratio in the randomized sub-study. Randomization will be stratified by diabetes mellitus (diabetic vs. non-diabetic), and lesion characteristics (complex vs. non-complex). Complex lesion characteristics include triple vessel treatment, or dual lesion per vessel treatment, or lesions involving RCA-aorto-ostial locations, or bifurcations lesions in which the side branch is  $\geq 2$  mm in diameter, or bifurcation lesions in which the ostium of the side branch is  $> 50\%$  stenosed. For patients enrolled in the randomized sub-study, once randomization is completed and a treatment is assigned, crossover is not permitted.

## **5 ENDPOINTS**

### **5.1 Primary Endpoint**

The following primary endpoint will be examined:

Adjudicated Composite rate of all Death, all Myocardial Infarction (MI) and Target Vessel Revascularization (TVR) at 1 year.

### **5.2 Secondary Endpoints**

The following secondary endpoints will be examined:

Acute Success (Clinical Device Success and Clinical Procedure Success)

Adjudicated Stent Thrombosis at 30 days, 240 days and at 1, 2, 3, 4 and 5 years (Definite, Probable, Possible)

Adjudicated revascularization (TLR/TVR/all revascularizations) at 30 days, 240 days and at 1, 2, 3, 4 and 5 years

Adjudicated Composite rate of Cardiac Death, MI attributed to the target vessel and CI-TLR at 30 days, 240 days and at 1, 2, 3, 4 and 5 years.

Adjudicated Composite rate of all Death, all MI and Target Vessel Revascularization (TVR) at 30 days, 240 days and at 2, 3, 4 and 5 years.

Adjudicated Composite rate of all Death, all MI and any Revascularization (TLR/TVR/non TVR) at 30 days, 240 days and at 1, 2, 3, 4 and 5 years.

Adjudicated Cardiac Death, Non-Cardiovascular Death, Vascular Death, Q-wave MI and Non Q-wave MI (Peri-Procedural, Unrelated to PCI) at 30 days, 240 days and at 1, 2, 3, 4 and 5 years.

In-stent Late Loss (LL) at 270 days (*main* secondary endpoint for the randomized sub-study)

In-segment Late Loss (LL) at 270 days (for the randomized sub-study)

In-stent and in-segment Angiographic Binary Restenosis rates at 270 days (randomized sub-study)

In-stent and in-segment percent Diameter Stenosis at 270 days (randomized sub-study)

Aneurysm, thrombus and persisting dissection at 270 days (for the randomized sub-study)

Additional analysis of specific female demographics such as menopausal, hysterectomy and oophorectomy status, past and current use of hormonal contraceptives, and use of weak estrogens will be outlined in the Statistical Analysis Plan (SAP).

## **6 SELECTION AND WITHDRAWAL OF PATIENTS**

### ***6.1 Patient Population***

Patients enrolled into this Clinical Evaluation will be comprised of female patients derived from the general interventional cardiology population. The Clinical Evaluation will enroll a total of approximately 2000 ‘real world’ patients who are screened in accordance with the commercial IFU of the XIENCE EECSS and who meet all eligibility criteria and have provided written informed consent.

### ***6.2 Patient Screening***

Patients planned to be admitted for a percutaneous coronary artery revascularization procedure should be screened for Clinical Evaluation eligibility by a member of the research team previously trained to the clinical investigation plan. Patients who do not satisfy inclusion and exclusion criteria will not be enrolled in this clinical evaluation. After meeting the general inclusion and exclusion criteria, patients will be asked to sign an informed consent. All patients who have signed an informed consent will be entered into the Screening log in InForm. (Refer to Appendix VI, Screening Process)

#### **6.2.1 Informed Consent**

Informed Consent needs to be signed and dated by the investigator and the patient or by her legal representative before any study-related procedure and before the pre-procedure angiographic screening procedure. The investigator or a person designated by the investigator who has been trained on the clinical investigation plan, will explain the nature and scope of the clinical evaluation, potential risks and benefits of participation, and answer the patient’s questions. If the patient agrees to participate, the informed consent form must be completed, signed and personally dated by the patient or legally authorized representative. A copy of the completed informed consent form must be provided to the patient. The obtaining of the consent, provision of a copy to the subject, along with the date and time should be documented in the subject’s medical records and signed by the investigator.

All patients must provide informed consent in accordance with the local Medical Ethics Committee (MEC) requirements, using an MEC-approved informed consent form. Appendix VI outlines the screening process and illustrates the point where informed consent should be obtained.

#### **6.2.2 Ethical Considerations**

This study will be conducted in accordance with the Declaration of Helsinki, BS EN ISO 14155-1:2003 and BS EN ISO 14155-2:2003 standards provided these do not oppose the applicable law. The conduct of the study will be approved by the appropriate MEC of the respective clinical site and as specified by local regulations.

### 6.3 Allocation of Patients to the SPIRIT WOMEN Single Arm Study and Randomized Sub-study

Up to 35 selected sites will participate in both the randomized sub-study and the Single Arm Study. In order to avoid bias in the population of the SPIRIT WOMEN Clinical Evaluation, these 35 sites will only recruit patients into the randomized sub-study, and not into the SPIRIT WOMEN Single Arm Study, during the recruitment period of the randomized sub-study. These sites can enroll all eligible patients into the SPIRIT WOMEN Single Arm Study outside of recruitment period of the randomized sub-study.

**Figure 6.3: Allocation of Patients**

[figure not shown]

### 6.4 Eligibility Criteria

Patients must meet **ALL** of the inclusion criteria to be considered for the clinical evaluation. If **ANY** of the exclusion criteria are met, the patient is excluded from the clinical evaluation and cannot be enrolled.

#### 6.4.1 General Inclusion Criteria

- Patient must be female.
- Patient must be at least 18 years of age.
- Patient is able to verbally confirm understanding of risks, benefits and treatment alternatives and she or her legally authorized representative provides written informed consent prior to any study related procedure, as approved by the appropriate Medical Ethics Committee of the respective clinical site.
- Patient must have evidence of myocardial ischemia (e.g., stable or unstable angina, silent ischemia, positive functional study or a reversible change in the electrocardiogram (ECG) consistent with ischemia).
- Patient must be an acceptable candidate for coronary artery bypass graft (CABG) surgery.
- Patient must agree to undergo all CIP-required follow-up examinations.
- Patients of childbearing potential must have had a negative pregnancy test within 7 days before treatment, and must not be nursing at the time of treatment.

#### 6.4.2 Angiographic Inclusion Criteria

- Patients' artery morphology and disease is suitable to be optimally treated with a maximum of 4 planned study stents.

- Target lesions must be de novo lesions (no prior stent implant, no prior brachytherapy).
- Target vessel reference diameter must be between 2.5 mm and 4.0 mm by visual estimate. The diameter range will be expanded to 2.25 mm when the 2.25 mm stent is available.
- Target lesion  $\leq$  28 mm in length by visual estimate.

#### **6.4.3 General Exclusion Criteria**

- Patient has other medical illness (e.g., cancer or congestive heart failure) or known history of substance abuse (alcohol, cocaine, heroin etc.) that may cause non-compliance with the clinical investigation plan, confound the data interpretation or is associated with a limited life expectancy (i.e., less than one year).
- Patient has a known hypersensitivity or contraindication to aspirin, either heparin or bivalirudin, both clopidogrel and ticlopidine, sirolimus, everolimus, cobalt, chromium, nickel, tungsten, acrylic and fluoro polymers or contrast sensitivity that cannot be adequately pre-medicated.
- Participation in another device or drug study or has completed the follow-up phase of another study within the last 30 days.
- Patient who is judged to have a lesion that prevents complete inflation of an angioplasty balloon.
- Patient has had a previous stent implant, either Bare Metal Stent (BMS) or Drug Eluting Stent (DES) within the target vessel(s)

#### **6.5 Patient Discontinuation**

Patients are considered enrolled in the study from the time of Registration or Randomization. Every patient should remain in the clinical evaluation until completion of the required follow-up period, however, a patient's participation in any clinical evaluation is voluntary and the patient has the right to withdraw at any time without penalty or loss of benefit. Should this occur, the reason for withdrawal must be documented in the source documentation. Conceivable reasons for discontinuation may include, but not be limited to, the following:

**Patient Withdrawal:** Patient participation in a clinical investigation is voluntary and the patient may discontinue participation (refuse all subsequent testing/follow-up) at any time without loss of benefits or penalty.

**Investigator Termination:** Investigator may terminate the patient's participation without regard to the patient's consent if the Investigator believes it is medically necessary.

**Lost-to-Follow-up:** Patient does not complete the scheduled follow-up visits but has not 'officially' withdrawn from the clinical evaluation. (Does not apply to missed visits). Site personnel should make all reasonable efforts to locate and communicate with the patient, including the following, at each contact time point:

- A minimum of two telephone calls to contact the patient should be recorded in the source documentation, including date, time, and initials of site personnel trying to make contact.
- If these attempts are unsuccessful, a certified letter should be sent to the patient and/or the patient's General Practitioner/Family Doctor. (this should be done only when the patient has consented to direct contact with General Practitioner/Family Doctor)
- If a patient misses one or more of the follow-up contact time points it will be considered a missed visit. Patient may then return for subsequent visits. If the patient misses two

consecutive time points and the above-mentioned attempts at communicating with the patient are unsuccessful, the patient will be considered lost-to-follow-up.

A Study Completion form must be completed when,

- the patient is considered lost to follow-up per the above definition or
- the patient withdraws from the Clinical Evaluation or
- the investigator withdraws the patient from the Clinical Evaluation or
- the patient has died or
- upon Clinical Evaluation completion (5 year follow-up time point has been reached)

Sponsor must be notified of the reason for patient discontinuation. The site will provide this information on the eCRF. Investigators must also report this to their MEC as defined by their institution's procedure. Patients will not be replaced.

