### *8.1 Clinical Follow-up for All Patients*

Clinical follow-up will be performed periodically at the following intervals for all patients:

30 days  $\pm$  7 days follow-up telephone contact/office visit

240 days  $\pm$  14 days follow-up telephone contact/office visit

1 year  $\pm$  28 days follow-up telephone contact/office visit

2 year  $\pm$  28 days follow-up telephone contact/office visit

3 year  $\pm$  28 days follow-up telephone contact/office visit

4 year  $\pm$  28 days follow-up telephone contact/office visit

5 year  $\pm$  28 days follow-up telephone contact/office visit

The following information will be collected at each of the time points:

Assessment of anginal status

Data regarding adverse events\*, including related laboratory tests, medications and/or ECGs

\* Following the 2 year follow-up, it is mandatory only to report and collect information on serious adverse events, cardiac adverse events and device related events.

Details of any subsequent repeat coronary angiography and results of such, if applicable

Details of any subsequent coronary interventions (e.g., repeat PCI or CABG)\*\*

Use and compliance of medications to clinical investigation plan (Aspirin and Clopidogrel)

Use and changes in chronic concomitant medications

\*\*All TLR in the Single Arm Study will be clinically indicated.

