## ***8.4 Serious Adverse Events***

Each adverse event or complication meeting the definition for serious adverse event **whether or not considered device-related** should be considered as such and reported to Sponsor **within 24 hours of knowledge of event by entering the event into the electronic database**. The completion of an Adverse Event / Serious Adverse Event (AE/SAE) form in the eCRF will trigger an e-mail notification to Sponsor containing the event information. The investigator will report the event to the EC according to the institution's reporting requirements.

Reports relating to the patient's subsequent medical course must be submitted to Sponsor until the event has subsided or, in case of permanent impairment, until the event stabilizes and the overall clinical outcome has been ascertained.

Sponsor will ensure that all SAEs are reported to the relevant authorities and Principal Investigators according to relevant regulations and that product experience handling reporting requirements are followed.

Note: All device malfunctions should be reported to the Sponsor within 24 hours of knowledge.

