### ***9.6 Procedures for Accounting for Missing Data***

Analyses will be based on available data, missing data excluded. Any unused or spurious data will be noted as appropriate in the final report.

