## **12.2 Associated Risks of Everolimus**

Everolimus is extensively metabolized by the cytochrome P4503A4 (CYP3A4) in the gut wall and liver and is a substrate for the countertransporter P-glycoprotein. Therefore, absorption and subsequent elimination of everolimus may be influenced by drugs that affect these pathways. Everolimus has also been shown to reduce the clearance of some prescription medications when it was administered orally along with cyclosporine (CsA). Formal drug interaction studies have not been performed with XIENCE Everolimus Eluting Coronary Stent System. Therefore, due consideration should be given to the potential for both systemic and local drug interactions in the vessel wall when deciding to place the XIENCE Everolimus Eluting Coronary Stent in a subject taking a drug with known interaction with everolimus.

Everolimus, when prescribed as an oral medication may interact with the following drugs:

- CYP3A4 isozyme inhibitors (ketoconazole, itraconazole, ritonavir, erythromycin, clarithromycin, fluconazole, calcium channel blockers)
- Inducers of CYP3A4 isozyme (rifampin, rifabutin, carbamazepin, Phenobarbital, phenytoin)
- Antibiotics (ciprofloxacin, ofloxacin)
- Glucocorticoids
- HMGCoA reductase inhibitors (simvastatin, lovastatin)
- Digoxin
- Cisapride (theoretical potential interaction)
- Sildenafil (Viagra®) (theoretical potential interaction)
- Antihistaminics (Terfenadine, astemizole)
- Grapefruit juice

Long term outcome for this permanent implant containing polymers and everolimus is unknown at present. Judicious selection of patients is necessary since the use of this device carries the associated risk of subacute thrombosis, vascular complications and / or bleeding events. Oral administration of everolimus in combination with cyclosporine have been associated with increased serum cholesterol and triglycerides. Therefore, patients should be monitored for changes in lipid profiles. Persons allergic to L-605 cobalt chromium alloy, acrylic or fluoro –polymers, or everolimus may suffer an allergic reaction to this implant.

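### Section 6.5 lets the investigator end a patient's participation on medical grounds and nothing keeps endpoint follow-up going afterwards, so the 1-year event rate can be biased downward

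*Protocol*

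**What the plan says.** Section 6.5 sets a general rule, "Every patient should remain in the clinical evaluation until completion of the required follow-up period", and then lists reasons for discontinuation. One is Investigator Termination: "Investigator may terminate the patient's participation without regard to the patient's consent if the Investigator believes it is medically necessary". No criteria are given. The section goes on to list when a Study Completion form is due, and one trigger is that "the investigator withdraws the patient from the Clinical Evaluation or". The others are death, patient withdrawal, loss to follow-up and reaching 5 years. The sponsor must be told the reason, investigators also report it to their ethics committee, and patients are not replaced.

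Section 8.1 allows every clinical contact to be by telephone or office visit. The entries from 1 to 5 years each allow "28 days follow-up telephone contact/office visit", and the 30-day and 240-day entries offer the same choice. Section 12.2 says of the device: "Long term outcome for this permanent implant containing polymers and everolimus is unknown at present".

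The primary endpoint in section 5.1 is the "Adjudicated Composite rate of all Death, all Myocardial Infarction (MI) and Target Vessel Revascularization (TVR) at 1 year". Section 9.6 gives the missing-data rule: "Analyses will be based on available data, missing data excluded".

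**The concern.** The study device is placed at the index procedure. After discharge, participation consists of clinical contacts and, in the randomized sub-study, one angiogram at 270 days. A medical reason may bear on a study procedure. It does not by itself prevent a site from finding out, by telephone or from records, whether the patient is alive or has had an MI or a revascularization. Section 6.5 does not separate the two: it ends participation.

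A patient removed because she is deteriorating may be at higher risk of the endpoint than those who stay. If she has had no endpoint event by then, and a later one is not captured, available-data analysis leaves her out and the observed rate falls. The secondary endpoints run to 5 years, so the same loss can accumulate, and long-term information on a permanent implant would be missing for some of the patients in whom it matters most.

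**Working it through.** **Does any section keep follow-up going?**

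- Section 6.5, Lost-to-Follow-up: at least two telephone calls, then a certified letter. No similar duty is stated for a patient terminated by the investigator.
- Section 8.2: a patient who does not need the 270-day film still continues her clinical visits. The protocol therefore already separates the film from clinical follow-up, but does not do so in 6.5.
- Section 11.2.3: follow-up of enrolled patients continues per protocol, but this concerns early termination of the whole study.
- Section 8.4, for SAEs: "Reports relating to the patient's subsequent medical course must be submitted to Sponsor until the event has subsided", or until the event stabilises. This follows an event already reported. It does not seek a new death, MI or TVR later on.

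No section requires endpoint follow-up after investigator termination.

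**The plan's own precision figure.** Section 9.2 gives N = 1550, a true rate between 10% and 14%, and a 95% half-width of 1.5% to 1.7%. With half-width = 1.96 × √(p(1 − p)/N):

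- p = 0.10: 1.96 × √(0.09/1550) = 1.49 points
- p = 0.14: 1.96 × √(0.1204/1550) = 1.73 points

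The stated figure reproduces.

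**Possible bias.** Let p be the true 1-year rate, q the share removed before any event, and r their event risk. The observed rate is (p − q·r)/(1 − q), so the bias is −q(r − p)/(1 − q). The documents give neither q nor r; both are assumptions. I take p = 12%, the middle of the planned range, and r = 50%.

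- q = 0.5% (about 8 of 1550): (0.12 − 0.0025)/0.995 = 11.81%, bias −0.19 points
- q = 1% (about 16 of 1550): (0.12 − 0.005)/0.99 = 11.62%, bias −0.38 points
- r = p, any q: bias 0

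**Outer bound.** Section 9.2 expects 3% drop-out at 1 year (0.03 × 1550 = 46.5 patients). If all of it were investigator termination before an event, which is an extreme assumption:

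| True rate | r = true rate | r = 30% | r = 50% | r = 100% |
|---|---|---|---|---|
| 10% | 0 | −0.62 | −1.24 | −2.78 |
| 14% | 0 | −0.49 | −1.11 | −2.66 |

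Continued follow-up would leave N and the planned half-width unchanged.

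**The case against.** The strongest reply is that this is a missing clarification with a narrow route to bias. The patient must be seriously ill, have had no endpoint event, be terminated, and then have an event that SAE follow-up does not capture. A serious deterioration would normally already be a reported SAE, so section 8.4 keeps its course reportable, and section 8.3.2 has adverse events monitored until resolved or explained. If the deterioration is itself an MI or leads to TVR, it already counts. Time-to-event variables are also shown by Kaplan-Meier (section 9.4), which keeps time up to exit, although informative censoring would remain possible. All of this stands, and it limits the likely size. It does not remove the gap: a new endpoint event after termination has no stated route into the data, and an SAP cannot recover outcomes that were never collected.

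Some stronger readings are tempting but not supported:

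- **That section 6.5 contradicts itself.** The rule that every patient should remain is followed in the same sentence by a qualification and then by listed exceptions.
- **That section 8.4 conflicts with termination.** It is a partial safeguard.
- **That the protocol expressly closes all follow-up.** Only Patient Withdrawal is glossed as refusing all further testing and follow-up. For Investigator Termination, closure is an inference from the end of participation, the form and the absence of any continuation rule.
- **That the randomized comparison is materially distorted.** Unequal use by arm cannot be excluded, but the primary endpoint is descriptive and sub-study success rests on in-stent late loss alone, which this change would not help. The documents support no arm-specific figure.

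**Conclusion.** The point holds as a gap in outcome follow-up. Section 6.5 permits an investigator-initiated exit that can be related to the primary endpoint, nothing requires endpoint follow-up afterwards, and section 9.6 works from available data. The 1-year rate can therefore be biased downward. The text leaves this possibility open; it does not direct the removal of the sickest patients.

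The size is unknown. Under the assumed 0.5% to 1% removal and 50% risk against 12%, it is about 0.2 to 0.4 points in the single arm study, at most about a quarter of the planned half-width. It is zero if removal is unrelated to risk. Values above 1 point need the whole planned drop-out to be investigator terminations at high risk. The case for change rests on its low cost. It takes no position on when a procedure should be withheld.

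**What to change.** Add to section 6.5 that an investigator's medical decision to end study procedures does not end outcome follow-up. Telephone or record follow-up for death, MI, revascularization, stent thrombosis and SAEs continues to 5 years unless the patient herself withdraws consent. Keep recording the investigator's decision and its reason on the eCRF, but do not treat that entry as the end of follow-up; the Study Completion wording in 6.5 should be aligned with this.

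The cost is a wording change, a matching adjustment to the eCRF, and telephone or record contacts for what is likely to be a small number of patients. No new procedure is needed, and neither the sample size nor the analysis changes.
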